## Abstract

**Background:**

Women with breast cancer face many barriers to returning to work (RTW) after their treatment. The Facilitating and Sustaining the Return to Work After Breast Cancer (FASTRACS) intervention aims to facilitate and sustain functional RTW.

**Objective:**

The main objective of the RECOVA-FASTRACS (Realist Collaborative Evaluation of a Work Disability Prevention Program for Breast Cancer Survivors) study is to evaluate the processes using a realist approach that analyzes what works, how, for whom, and under what circumstances.

**Methods:**

The RECOVA-FASTRACS study uses a mixed methods design to assess the implementation, context, and impact mechanisms of the FASTRACS intervention. The qualitative analysis will include 2 main components: a trajectory analysis and a focus group assessment. The trajectory analysis will examine the experiences of women who participated in the intervention and key individuals involved in their RTW process. We will use semistructured interviews according to the multiple-case study method. Additionally, to explore organizational and professional practices, focus groups will be conducted with professionals who deliver the intervention. To analyze the trajectories, embedded and iterative integration will combine the qualitative findings with relevant quantitative data from the FASTRACS randomized controlled trial for 5 domains: personal situation, professional situation, RTW, care pathway, intervention tool use, and perceived usefulness.

**Results:**

The RECOVA-FASTRACS study received funding in 2022. Recruitment and qualitative data collection began in month 6. Final analyses are expected to be completed by the end of 2026, with dissemination of the main findings anticipated in late 2027.

**Conclusions:**

Our mixed methods realist evaluation will provide a detailed analysis of the intervention processes, helping to identify impact mechanisms within specific contexts. This approach is meant to ensure a more informed and realist deployment of the intervention by professionals following the study.

## Introduction

### Background

In Europe, 5.4 million women were living with breast cancer in 2020 [1]. In France, more than 61,000 new cases are diagnosed every year, half of them in women of working age [2]. More than 254,000 patients diagnosed with breast cancer in the past 5 years are still alive [3]. While the incidence of breast cancer continues to rise, especially among women under the age of 50 years [4], the retirement age continues to increase. Consequently, returning to work (RTW) after breast cancer is essential for women wishing to resume a professional life [5], ensuring their financial independence and social participation while reducing the social costs associated with the disease [3].

However, research has identified several obstacles that impede women’s RTW [6,7]. These obstacles are associated with the consequences of the disease and its treatment (fatigue, pain, and cognitive problems) and the age of the patients [8,9]. Interprofessional collaboration could effectively support these patients in the postcancer phase, but barriers continue to hinder collaboration between breast cancer specialists, general practitioners, and occupational physicians [10]. In the work environment, professional demands may not be compatible with the patients’ situations. Moreover, a lack of knowledge about the disease, along with insufficient support from superiors and colleagues, may complicate RTW [11,12]. Sociodemographic inequalities also influence RTW, with a less favorable occupational prognosis in older and less-qualified people [13,14].

The importance of RTW has been formalized in France’s 10-year cancer strategy for 2021 to 2030 [15]. Employers are implementing measures to support employee reintegration, including the “Cancer and Employment” charter established by the French National Cancer Institute. The charter seeks to provide additional assistance for individuals undergoing or recovering from cancer treatment [16].

Multidisciplinary interventions appear to increase the number of people who RTW [17]. These interventions are filling the gaps left by overly medicalized interventions, which have been criticized for their weak theoretical basis. Such a basis has proved insufficient for analyzing the causes (problem theory) of obstacles and for proposing solutions (action theory) [18,19].

The Facilitating and Sustain the Return to Work After Breast Cancer (FASTRACS) research program [20] was developed using the intervention mapping framework [21]. It addresses the need for multidisciplinary interventions [22] by engaging various RTW stakeholders early in the cancer care process. The intervention consists of an RTW pathway for breast cancer survivors (BCSs) that connects the hospital, the primary care team, and the workplace environment, starting when active treatments have concluded [20]. This pathway is structured around 4 tasks for supporting BCSs:

Regularly assess their needs and find relevant information using the patient guide specifically created for this purpose [23].Schedule an appointment dedicated to RTW anticipation with their general practitioner.Schedule an appointment with their occupational physician.Maintain or reestablish contact with their workplace environment.

With these tasks completed, BCSs can anticipate the potential professional challenges associated with RTW and optimize their comeback.

However, the process of change cannot rely on women alone and must target the behaviors of other stakeholders as well (eg, general practitioners, occupational physicians, managers, and so on), in line with the recommendations on complex interventions [24]. Four tools have thus been developed to facilitate the process, mobilizing the key actors in the RTW process:

A *patient guide* structured in 3 sections: an informative section detailing 4 key tasks to prepare for RTW, a personal development section to support this process and prevent difficulties, and a resource directory listing relevant services and tools.A *checklist for the general practitioner* to standardize the assessment of needs, the design of post–breast cancer care, and the RTW plan.A *checklist for the occupational physician* to standardize the assessment of aptitude and the adaptation of the workstation to prepare for the RTW among BCSs.An *employer’s guide* to help local managers, human resources, employers, and occupational physicians understand the challenges of employee reintegration. It provides guidance on ensuring optimal working conditions, adapting job roles, facilitating internal job transitions when needed, and offering support for external career opportunities if necessary.

A randomized controlled trial (RCT) is currently underway (FASTRACS-RCT, NCT04846972) in 14 investigation centers. The trial will evaluate the effects of the FASTRACS intervention on the sustainable RTW of BCSs 12 months after the end of active treatment [25].

RTW interventions are considered complex interventions due to the diverse influencing factors, the multiple actors involved, and the variety of implementation contexts [26]. Such interventions have a heightened risk of failure in terms of delivery and sustainability due to the dynamic interactions among their components. To better anticipate these challenges, the Medical Research Council recommends evaluating these interventions to gain a contextualized understanding of how they induce changes while analyzing the factors that facilitate or hinder their delivery [26].

Therefore, in addition to conducting a quantitative evaluation of the effects, it is necessary to evaluate the intervention processes [27]. This process evaluation serves 3 key purposes: it provides a dynamic analysis of the intervention’s implementation, examines the mechanisms through which it generates impact, and identifies the contextual factors that influence these mechanisms.

### Objectives

The main objective of the RECOVA-FASTRACS (Realist Collaborative Evaluation of a Work Disability Prevention Program for Breast Cancer Survivors) study is to conduct a process evaluation of the FASTRACS intervention by examining its implementation, context, and impact mechanisms. More specifically, this ancillary study will assess what has been implemented and how, while identifying barriers and facilitators influencing the implementation of the intervention components. In parallel, the context analysis will explore how specific contextual factors affect the intervention’s implementation and outcomes. Finally, the study of impact mechanisms will examine how the intervention produces the expected effects and any unintended consequences that may arise.

The secondary objective is to refine the initial propositions of intervention theory by confirming or revising them through the elaboration of middle-range theories.

## Methods

The reporting of the study protocol follows the RAMESES II (Realist And Meta-narrative Evidence Syntheses—Evolving Standards) reporting standards for realist evaluation and the GRAMMS (Good Reporting of a Mixed Methods Study) guidelines (Checklist 1) [28,29].

### Realist Evaluation as a Process Evaluation Approach

Process evaluation can be carried out using various methodological approaches. Among these, realist evaluation [30,31] stands out for its systematic approach to the interactions between intervention and context. Stemming from the theory-based evaluation movement [32], realist evaluation aims to answer the question of “what works, how, why, for whom, and in what circumstances” [30] by identifying context-mechanism-outcome (CMO) configurations. By analyzing these configurations together, researchers can define “demi-regularities” and develop middle-range theories that explain the variations in observed effects [33]. By comparing these theories with the intervention’s initial assumptions in the theory of intervention, the researcher can refine the intervention theory. Applying this approach to the FASTRACS intervention makes it possible to dynamically analyze its implementation and impact mechanisms, supporting its future adaptation and scalability in real-life settings.

### Study Design

RECOVA-FASTRACS is a realist process evaluation conducted as a mixed methods ancillary study to FASTRACS-RCT to refine the initial program theory (publication forthcoming and Broc et al [23]). In this study, the mixed methods approach refers to the integration of qualitative and quantitative data within the overarching realist evaluation framework. It uses a convergent design within a case-study framework [34]. The study integrates theory-testing interviews through a multiple-case study with quantitative data from FASTRACS-RCT using an embedded approach to triangulate findings.

The qualitative research will be divided into 2 parts:

Substudy A: a study of the trajectories of the BCSs who have completed follow-up in the FASTRACS-RCT intervention group (RCT-I). This study aims to analyze the RTW pathway of these participants, examining the role of the intervention in this process.Substudy B: a study focusing on the professionals involved in the FASTRACS-intervention delivery.

In substudy A, we will analyze the trajectories of RCT-I, focusing on participants’ experiences of the intervention through their own narratives. These results will then be triangulated with those of the people who contributed to their RTW pathway. Data will be collected through semistructured interviews scheduled at the end of the RCT-I follow-up in FASTRACS-RCT to prevent contamination risks.

Simultaneously, substudy B will explore how professionals deliver the intervention. We will conduct focus groups to gather multiple perspectives, allowing for interaction on the topics discussed. This approach will facilitate the identification of organizational dynamics and professional practices specific to each professional [35].

In quantitative research (substudy C), we will analyze data from the RCT questionnaires completed by RCT-I.

Only participants from the intervention arm will be included in the qualitative trajectory analysis, as the objective of the realist evaluation is to explore the implementation processes, mechanisms, and contextual conditions associated with exposure to the FASTRACS intervention. The study does not aim to qualitatively compare intervention and usual-care trajectories. However, experiences related to usual care, RTW barriers, and the ordinary experience of living with breast cancer and RTW have already been extensively explored during the needs assessment phase of the intervention mapping process [20]. In addition, the profession-specific focus groups conducted with professionals involved in RTW support will contribute to documenting routine professional practices and usual-care conditions experienced by women participating in the FASTRACS-RCT. Quantitative data from the FASTRACS-RCT, including participants from both intervention and usual-care groups, will further support contextualization and interpretation of the intervention-specific mechanisms identified through the realist analysis.

Triangulation of qualitative findings with quantitative data will allow the formulation of hypotheses on the implementation, underlying contexts, mechanisms, and effects that the intervention might produce on the RCT-I. Figure 1 illustrates the design of the study.

**Figure 1. F1:**
[figure not shown]
RECOVA-FASTRACS (Realist Collaborative Evaluation of a Work Disability Prevention Program for Breast Cancer Survivors) study design. RCT: randomized controlled trial.

### Recruitment Process and Sampling Strategies of Studies

#### Substudy A: Trajectory Analysis

To explore the various experiences of those participating in the intervention, RECOVA-BCS will constitute a sample of typical cases [36] among RCT-I as “the most representative of the phenomenon being explored.” It will refer to the most frequently observed profiles identified during sampling and early analysis, representing recurrent RTW trajectories within the dataset. This RECOVA-BCS sampling will then be conducted to construct a theoretical sample that maximizes variation based on factors, such as age, occupation, and place of residence.

RECOVA-BCS selected for the study will be asked for permission to interview individuals who helped them in their RTW pathway. This population is divided into 2 groups:

Program theory actors (PTAs): general practitioners, occupational physicians, and workplace stakeholders, who have been preidentified as key actors in the RTW pathway and are directly involved in the intervention through specific tools (such as checklists and employer’s guide).RTW supporters: individuals identified by RECOVA-BCS participants as having provided significant support during the post–heavy treatment period and RTW. They can include health professionals (eg, physiotherapists and nurses), workplace individuals (eg, colleagues), and up to 3 relatives.

Due to the iterative nature of qualitative methodology, sampling of RECOVA-BCS, PTAs, and RTW supporters will be progressively guided by the initial program theory of the FASTRACS intervention (publication forthcoming), translated into intervention-context-actor-mechanism-outcome (ICAMO) configurations. Sampling will aim to ensure sufficient variation to test and refine this theory across different contexts as the analysis evolves. Data collection will be carried out until saturation is reached [37], defined as the point at which ICAMO configurations are sufficiently stable and no further refinement of the program theory emerges from additional cases, including situations where expected mechanisms are not activated in specific contexts.

We anticipate including approximately 20 RECOVA-BCS in individual interviews over time to gather sufficient information on how the intervention is experienced by a large diversity of profiles. This sample size aligns with qualitative and realist-informed studies. For each RECOVA-BCS, interviews will also be conducted with up to 4 individuals involved in their RTW support, including at least one PTA, allowing for the triangulation of perspectives across key actors involved in the RTW process. We expect to identify between 10 and 15 theoretical pathways (ie, the patient and 1 PTA) to maximize the diversity of RTW trajectories. However, this is an iterative process, and the reality on the ground may lead us to revise our initial sampling.

At the end of the FASTRACS-RCT, deviant and crucial cases [36] may be identified and included to deepen the understanding of the intervention and its mechanisms. These cases will be identified through the quantitative component of the study, based on results that appear atypical or particularly informative in relation to the questionnaire data. This may include extreme values, as well as trajectory patterns identified through cluster-based analyses distinguishing groups with faster versus more delayed RTW processes.

#### Substudy B: Professionals Delivering the Intervention

To analyze how the intervention is implemented, professionals delivering the intervention will be identified at every stage of the FASTRACS intervention, including professionals such as the RCT participants (oncologists and clinical research associates), general practitioners, occupational health teams (occupational physicians or occupational nurses), and staff from the Regional Center for Occupational and Environmental Pathologies. Sampling will be theoretical and aims to maximize variation in characteristics, such as age, gender, professional role, geographical area, and the number of BCSs included in the RCT they supported.

The categories of professionals are as follows:

Oncologists: physicians who have enrolled BCSs in the FASTRACS-RCT.Clinical research associates: those tasked with delivering the intervention tools to RCT-I.General practitioners: physicians providing care to RCT-I, identified through the RCT database.Occupational health teams: teams identified through the RCT database, including those from the Regional Center for Occupational and Environmental Pathologies.

Approximately 10 profession-specific focus groups are expected to be conducted to capture a wide range of perspectives on the implementation of the intervention, particularly regarding contextual conditions and intervention delivery across settings and professional categories. When group constitution proves difficult due to recruitment or scheduling constraints, semistructured individual interviews will be conducted instead.

The number of focus groups will depend on data saturation [37] under a realist perspective defined here as the point at which no new ICAMO configurations related to implementation processes, contextual influences, or professional responses emerge, and when additional data no longer contribute to the refinement of the program theory.

#### Substudy C: Quantitative Data

In this mixed methods study, quantitative data will be drawn from the FASTRACS-RCT questionnaires that were administered to RCT-I. The characteristics of this study population are detailed in the FASTRACS-RCT protocol [25].

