### Quantitative Data Integration

Quantitative data from FASTRACS-RCT surveys (collected at baseline, 4, 8, and 12 mo) will be analyzed following the prespecified statistical analysis plan [25]. In addition, subgroup analyses (eg, by socioprofessional category, age, center, and company size) will be used to test the hypotheses developed during the interviews.

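### The article gives conflicting accounts of which trial arms supply the quantitative data, so its subgroup analyses could be run on a population that cannot show differential benefit

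*Protocol article*

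**What the plan says.** Five places in the protocol article bear on who enters the quantitative analysis.

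- **Study Design**, on substudy C: "we will analyze data from the RCT questionnaires completed by RCT-I". The same section defines RCT-I as intervention-group survivors who completed follow-up, so the label means one arm and completers only.
- **Recruitment Process and Sampling Strategies, Substudy C**: "quantitative data will be drawn from the FASTRACS-RCT questionnaires that were administered to RCT-I".
- **Study Design**, a little later: "Quantitative data from the FASTRACS-RCT, including participants from both intervention and usual-care groups, will further support contextualization and interpretation" of the intervention-specific mechanisms.
- **Data Collection, Substudy C**: the interviewed women's trajectories will be compared with those of a broader FASTRACS-BCS population. That term is not defined by arm.
- **Quantitative Data Integration**: the survey data follow the trial's prespecified analysis plan and, in addition, "subgroup analyses (eg, by socioprofessional category, age, center, and company size) will be used to test the hypotheses developed during the interviews". Neither an arm nor a contrast is named.

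Two further sections give the purpose. Embedded and Iterative Integration aims at middle-range theories of who benefits, how and in what conditions. The Discussion expects quantitative findings to help pick out profiles of women who seem to benefit. The Background reports that RTW varies "with a less favorable occupational prognosis in older and less-qualified people".

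**The concern.** An analyst working from this text cannot tell whether the added subgroup analyses use one arm or two. The choice matters because the two populations answer different questions. Within the intervention arm, a subgroup difference in RTW shows who returned while receiving the intervention. Part of that difference would have been present under usual care, and part may reflect a larger effect in one group. One arm cannot separate the two.

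The article's own background makes the mixing predictable. It names age and qualification as prognostic for RTW, and age and socioprofessional category are two of the four example subgroup factors. At stake is whether an ordinary prognostic gradient gets written into the refined program theory as a finding about where the intervention works. The Discussion expects the results to inform decisions on scaling up.

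**Working it through.** **1. Is there a figure to reproduce?** No. The article gives no quantitative sample size, RTW rate, effect size or alpha, and refers to the trial protocol for the study population. The check is a comparison of the text, followed by an illustration whose rates are all assumed.

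**2. Text comparison.**

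| Place | Population stated |
|---|---|
| Study Design, substudy C sentence | RCT-I only |
| Sampling, Substudy C | RCT-I only |
| Study Design, paragraph on the choice of arm | Both arms |
| Data Collection, Substudy C | Not defined by arm |
| Quantitative Data Integration | Not stated; subgroup analyses are additional to the trial plan |

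Two statements say one arm, one says both, and two leave it open. Because the subgroup analyses are additional to the prespecified plan, that plan cannot be assumed to settle who is in them.

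**3. What a one-arm contrast identifies.** Let I1 and I2 be the intervention-arm RTW proportions in subgroups 1 and 2, and U1 and U2 the usual-care proportions.

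- One-arm contrast = I1 - I2.
- Interaction (difference in effects) = (I1 - U1) - (I2 - U2) = (I1 - I2) - (U1 - U2).

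The two differ by U1 - U2, the prognostic gap, which RCT-I does not contain. Assume I1 = 80% and I2 = 60%, so the one-arm contrast is always +20 points:

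| Usual care U1 / U2 | Effect in 1 | Effect in 2 | Interaction |
|---|---|---|---|
| 80% / 60% | 0 | 0 | 0 |
| 70% / 50% | +10 | +10 | 0 |
| 65% / 60% | +15 | 0 | +15 |
| 80% / 45% | 0 | +15 | -15 |

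Identical intervention-arm data fit all four rows.

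**4. How often a purely prognostic gap would look like a finding.** Take the first row, where the intervention has no effect in either subgroup. For a two-sided 5% two-proportion test with n women per subgroup:

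probability = Φ[(d - 1.96·SE0) / SE1], with d = 0.20, SE0 = √(2 × 0.70 × 0.30 / n) and SE1 = √((0.80 × 0.20 + 0.60 × 0.40) / n).

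At n = 100, SE0 = 0.0648 and SE1 = 0.0632, so (0.20 - 0.1270) / 0.0632 = 1.154 and the probability is 0.876. At n = 50 it is 0.590, and at n = 200 it is 0.993.

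A second assumed setting has the same +10-point effect in both subgroups, intervention-arm RTW of 70% in one and 80% to 90% in the other, and 100 to 250 women per arm split equally. Using the unpooled standard error, the probability runs from 0.213 (100 per arm, 10-point gap) to 0.983 (250 per arm, 20-point gap). It is 0.733 at 200 per arm and a 15-point gap. True effect modification is zero throughout.

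**5. Price of the valid contrast.** In the second setting with 200 per arm and a 15-point gap, intervention-arm RTW is 70% and 85%, and usual-care RTW is 60% and 75%.

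- SE(interaction) = √((0.70×0.30 + 0.85×0.15 + 0.60×0.40 + 0.75×0.25) / 100) = 0.0875.
- SE(overall effect) = √((0.775×0.225 + 0.675×0.325) / 200) = 0.0444.
- Ratio = 1.97; across gaps of 10 to 20 points it is 1.95 to 1.99.

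The interaction is thus about half as precise as the overall effect.

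**The case against.** The strongest reply is that no sentence confines the subgroup analyses to RCT-I. They are introduced directly after the trial's own analysis plan, the trial is designed to evaluate the intervention's effects, and Study Design explicitly brings in both arms to help interpret mechanisms. A two-arm reading is at least as plausible. This stands: a reader might infer that a one-arm subgroup analysis is the settled plan, and the document does not support that. What remains is the contradiction, and the two sentences that define substudy C give the answer that would mislead.

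Second, the stated purpose of the subgroup analyses is to test interview hypotheses. Some of these may concern tool use or implementation, where intervention-arm data are appropriate or the only data possible. This also stands. The link to who benefits is an inference from the integration section and the Discussion; it is reasonable, but the subgroup sentence does not state it.

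Third, this is a theory-generating realist evaluation resting on configurations from about 20 cases and on focus groups. A rule that no configuration may be described as working better for some women without an interaction test would go too far. That is accepted, and the fix is limited to quantitative claims of differential benefit on RTW. The intervention-only qualitative sample is justified in the article and is not questioned here.

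Fourth, interaction models belong in the trial's analysis plan, which is not shown. Their absence from the article is therefore not counted as a fault.

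**Conclusion.** The point holds as an internal contradiction with a conditional consequence. The population of substudy C is fixed as intervention-arm completers in two places and as both arms in another, with two places open. If the subgroup analyses followed the two definitions of substudy C, RTW differences by age or socioprofessional category would mix prognosis with differential benefit and could not support statements about who benefits.

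One might be tempted to say that intervention-arm data show only who would return to work anyway. That is too strong: they show who returns under the intervention, which combines prognosis and effect.

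No size can be attached to this study. The -15 to +15 point range and the probabilities of 0.59 to 0.99 and 0.21 to 0.98 rest wholly on assumed rates, gaps and subgroup sizes, and apply only under the one-arm reading. They show that the problem can be large, not that it is. The wording should be corrected before the quantitative and qualitative findings are integrated, but the defect does not invalidate the design.

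**What to change.** Reconcile the two statements in Study Design, the Substudy C paragraphs under sampling and data collection, and Quantitative Data Integration, so that each quantitative analysis names its arm or arms. Specifically:

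- State that any quantitative subgroup analysis of differential benefit on RTW uses all randomised women in both arms, not only those who completed follow-up. It should report arm-by-subgroup interaction estimates with confidence intervals and be labelled exploratory.
- Keep RCT-I-only data for tool use, perceived usefulness and implementation, reported descriptively.
- Define the FASTRACS-BCS comparison population by arm.

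The cost is wording and some analysis time. The Results section says trial follow-up ended in January 2026, so no new outcome data are needed, and integration is scheduled from month 54. The real downside is precision: the interaction intervals will be wide, and fewer positive statements about who benefits will be possible.
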